**Methods:**

Participants with physician-confirmed hand OA according to the ACR clinical criteria are being recruited from two Norwegian OA cohorts: the population-based “Musculoskeletal pain in Ullensaker Study” (MUST) OA cohort, and the hospital-based Oslo Hand OA cohort. Participants are randomised into an intervention- or control group. The control group receives “usual care”, whereas the intervention group receives a 12-week exercise intervention. The intervention group attends four group sessions and is instructed to perform the exercise program three times a week at home. Adherence will be captured using self-report. During the eight weeks with no group sessions, the intervention group receives a weekly telephone call. The assessments and group sessions are being conducted locally in Ullensaker Municipality and at Diakonhjemmet Hospital, Oslo. Outcomes are collected at baseline, and at 3 and 6 months. The primary outcome measure is self-reported hand activity performance at 3 months post-randomisation, as measured by the Functional Index for Hand Osteoarthritis (FIHOA); and a patient-generated measure of disability, the Patient-Specific Functional Scale (PSFS). Secondary outcome measures are self-reported OA symptoms (e.g. pain, stiffness and fatigue), the Patient Global Assessment of disease activity, measured hand function (e.g. grip strength, thumb web space and hand dexterity) and health-related quality of life. Cost-utility and cost-effectiveness analyses will be conducted.

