### Study objective

A randomised controlled trial (RCT) has been designed to investigate the effects of a 12-week exercise programme with telephone follow-up on self-reported hand activity performance among people with hand OA. Our hypothesis is that the intervention group will report better hand activity performance at the 3-month follow-up compared to the control group.

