### Outcome measures

The outcome measures have been selected based on those recommended for clinical trials in patients with hand OA [34,35], and consist of a combination of patient self-reported outcomes and performance tests. All outcome measures are collected at baseline, 3 months (post-intervention, primary endpoint) and 6 months (Tables 3 and 4). If a participant is unable to attend the assessment on the given date (i.e. due to vacation, sickness, etc.), a new appointment is made. For extraordinary situations (i.e. long-term vacation), the questionnaire is sent by mail/e-mail or the most important outcome measures (marked in Table 3) are collected in a telephone interview.

**Table 3 T3:** Primary and secondary outcomes

**Primary outcome measures:**	**Measurement scale**	**Time***
Hand activity performance (The Functional Index for Hand OsteoArthritis, FIHOA [36]) #	0-30	0, 3, 6
Patient-generated disability (Patient-Specific Function Scale, PSFS [37]) #	0-10	0, 3, 6

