### Primary outcome measures

The primary outcome measure is self-reported hand activity performance, as measured by the the Functional Index for Hand OsteoArthritis (FIHOA) [36] and the Patient-Specific Function Scale (PSFS) [37].

The FIHOA consists of 10 items with a four-point Likert scale: “possible without difficulty” (0), “possible with slight difficulty” (1), “possible with important difficulty” (2) and “impossible” (3). In this study, it is used as a patient self-administered instrument, and a total score is calculated, with 0 indicating a good performance and 30 indicating a very poor hand activity performance. The instrument has previously been translated from French to Norwegian using a forward-backward translation that followed recommended procedures [44], and evidence for test-retest reliability, validity and responsiveness has been shown [36,45,46].

The PSFS is a patient-specific instrument commonly used in assessments and evaluations in musculoskeletal pain disorders. The instrument is interview-administered, and the patient is asked to name three to five important activities that they are unable to do or have difficulty doing as a result of their problem (in the present study: their hand OA). The patient then scores the difficulty on an 11-point numeric rating scale (NRS), in which 0 represents “Unable to perform activity” and 10 “Able to perform activity at pre-injury/disease level”. The scores for each activity are used independently and no total score is calculated. In a recent systematic review, the instrument’s measurement properties have been found to be acceptable for several musculoskeletal disorders [47], and it was found to be responsive in patients with musculoskeletal disorders receiving physiotherapy treatment in primary care [48].

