An exploratory sub-group analysis will be completed to examine the effectiveness of the exercise programme for those participants attending all group sessions and performing all home sessions. This analysis will only be completed if there are sufficient participants attending all four treatment sessions and performing all home sessions. Treatment concordance will also be evaluated descriptively by self-reported exercise frequency and duration at the 3- and 6-month follow-up.

Exact analyses utilising the binominal distribution will be used to assess the success of outcome assessor blinding (with 95% confidence intervals); no statistical adjustment will be made for multiple testing, and all tests will be two-sided and carried out at the 5% level of significance. Any changes to the study design or analysis plan will be documented with full justification.

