### Sample size

The primary outcome measure FIHOA sum score (range: 0–30 points) was used to estimate sample size. Using a minimal clinically important change (MIC) of three points (10%) (sd 6.2), with a significance level of 0.05 (2 tailed) and a power of 80%, we estimated that 68 persons will be needed in each group. To allow for a 10% drop-out rate, 75 persons will be included in each group.

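### FIHOA and PSFS are both primary, each tested at 5% with adjustment ruled out and no rule for combining them; if either may win, the family-wise error is about 7–10%

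*Protocol article*

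**What the plan says.** The Study objective section gives one general hypothesis: "Our hypothesis is that the intervention group will report better hand activity performance at the 3-month follow-up compared to the control group".

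Two instruments carry it. The Primary outcome measures section says the outcome is measured by "the Functional Index for Hand OsteoArthritis (FIHOA) [36] and the Patient-Specific Function Scale (PSFS) [37". Table 3 lists PSFS under its primary heading as "Patient-generated disability (Patient-Specific Function Scale, PSFS [37", beside FIHOA. The abstract also names both and sets the time point: "The primary outcome measure is self-reported hand activity performance at 3 months post-randomisation".

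On testing, the Data analysis section says "no statistical adjustment will be made for multiple testing, and all tests will be two-sided and carried out at the 5% level of significance".

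Two further statements bear on the point:
- Sample size section: "The primary outcome measure FIHOA sum score (range: 0–30 points) was used to estimate sample size". PSFS does not enter the calculation.
- Primary outcome measures section, on PSFS, where each patient names three to five activities: "The scores for each activity are used independently and no total score is calculated".

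The article does not say whether one or both instruments must be significant, and it sets no order of testing.

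**The concern.** One primary conclusion can be reached by two routes, each open at the full 5%. The article does not merely leave multiplicity for later. It rules out adjustment for every test, and the primary pair is not exempted.

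Two things are at stake. First, the 5% level may not hold for the trial's main conclusion. Second, a split result has no agreed reading. If FIHOA is null and PSFS is significant, the text does not prevent a claim of success on the outcome that was not used for the sample size. If the rule is chosen after the results are known, it cannot be shown to be independent of them.

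**Working it through.** **Inputs from the article.** Two primary instruments; two-sided 5% per test without adjustment; a FIHOA difference of 3 points with SD 6.2, 80% power, 68 per group, and 75 per group after a 10% drop-out allowance.

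**Input not in the article.** The correlation between the FIHOA and PSFS test statistics. I assume a range of 0 to 0.9.

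**Step 1: reproduce the sample size.**
n per group = 2 × (SD/difference)² × (z₀.₉₇₅ + z₀.₈₀)² = 2 × (6.2/3)² × (1.960 + 0.842)² = 67.05, rounded up to 68. The stated figure reproduces. At 68 per group, power is 80.6% by the normal approximation and 80.0% by the noncentral t.

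**Step 2: family-wise error if either instrument suffices.**
For independent tests: 1 − (1 − 0.05)² = 9.75%. Whatever the correlation, the error cannot exceed 5% + 5% = 10%. For correlated tests I computed the probability that at least one |Z| exceeds 1.96 under a bivariate normal null. The last column counts only false claims in favour of exercise (at least one Z above 1.96), for which the nominal level is 2.5%.

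| Assumed correlation | Two-sided error | False claim favouring exercise |
|---|---|---|
| 0 | 9.75% | 4.9% |
| 0.3 | 9.5% | 4.8% |
| 0.5 | 9.1% | 4.5% |
| 0.7 | 8.3% | 4.2% |
| 0.9 | 7.0% | 3.5% |

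**Step 3: if each PSFS activity were tested beside FIHOA.**
Three to five activities plus FIHOA make four to six tests. For independent tests: 1 − 0.95⁴ = 18.5% and 1 − 0.95⁶ = 26.5%. At a common correlation of 0.5, simulation gives 15.5% and 20.7%. The article does not say that the activity scores will be tested this way, so these figures are conditional.

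**Step 4: what the alternatives cost.**
- *Both required.* The error is at most 5%, but the power to win on both cannot exceed the FIHOA power of 80%, and the article gives no joint power.
- *Alpha split at 0.025 each.* The error is at most 5% (1 − 0.975² = 4.94% if independent). FIHOA power at 68 per group falls to 71.0% by the noncentral t (71.9% by the normal approximation). Restoring 80% needs 2 × (6.2/3)² × (2.241 + 0.842)² = 81.2, so 82 per group, or 82/0.9 = 91.1, so 92 per group with drop-out.
- *FIHOA first, PSFS only if FIHOA is significant.* The error over the pair is 5%, and FIHOA keeps its 80.0%.

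**The case against.** The strongest reply is that the inflation depends on a reading the article never states. The primary outcome is in the singular, measured by one instrument and the other, and there is a single hypothesis. A both-required reading is therefore open, and under it no adjustment is needed. This stands: a reader might infer that the plan's true error is 9–10%, but the documents do not establish it. That figure needs the either-wins rule and a correlation of no more than about 0.5. Both instruments measure hand activity performance in the same patients, so a higher correlation is plausible.

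A reader might also call PSFS unpowered. The article gives no target effect or SD for PSFS, so its power is unknown, not shown to be low. All that can be said is that PSFS was not used for the sample size.

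A further reply is that a rule for combining two primaries may sit in the full protocol or SAP, which are not shown. That is fair for the missing rule taken alone. It does not cover the express sentence that excludes adjustment for all tests, and the point rests on that sentence.

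Sizing on FIHOA does not settle the matter either. The Sample size section says which measure was used in the calculation. It does not demote PSFS or give FIHOA precedence in testing.

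Finally, leaving outcomes unadjusted can be defended in a pragmatic trial. I accept that for the secondary and tertiary outcomes, but not for two co-equal routes to one primary conclusion.

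**Conclusion.** The point holds conditionally. Two outcomes are declared primary for one hypothesis, each is tested at two-sided 5%, adjustment is expressly ruled out, and no order or both-required rule is given. If significance on either is taken as success, the two-sided error is about 7–10% instead of 5%. For false claims favouring exercise it is about 3.5–4.9% against a nominal 2.5%. These ranges rest on the either-wins rule, which is permitted but not stated, and on an assumed correlation between 0 and 0.9. Separate testing of the PSFS activities would raise the error further. If both outcomes were required, there would be no inflation. On either reading, the decision rule has to be written down.

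**What to change.** Before unblinding:

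1. Name FIHOA at 3 months as the lead primary, tested at two-sided 5%. It already carries the sample size.
2. Define one PSFS summary per patient, for example the mean over the activities nominated at baseline, and amend the statement that no total is calculated. Without this there is no single PSFS variable to put in a testing order.
3. Test that summary confirmatorily at two-sided 5% only if FIHOA is significant.
4. Limit the no-adjustment sentence to the remaining outcomes and label them supportive.
5. Record the change with its justification, as the Data analysis section requires for any change to the analysis plan.

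Cost: PSFS, whose power is not stated, can no longer carry the primary claim alone, and changing the standing of a declared primary in a running trial needs an open explanation. The sample size and the FIHOA power (80% at 68 per group) do not change. Requiring both outcomes or splitting alpha would also hold 5%. The first leaves the power for success unstated, and the second lowers FIHOA power to about 71%, so ordering is the cheaper repair.

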### Health economics

Based on the findings in this study two economic evaluations will be conducted, applying both health system and societal perspective. Costs in the health-care sector comprise intervention costs and costs related to treatment and follow-up, while societal costs include production loss, as well as costs for the individuals and the family. The primary economic evaluation will be cost-utility analysis (CUA) of the cost per extra quality adjusted life years (QALYs), which will be calculated using the 15D scores at 3 and 6 months. The secondary evaluation will be a cost-effectiveness analysis (CEA) based on the disease-specific measure FIHOA. Incremental cost per QALY (cost per FIHOA) will be calculated as the ratio of the difference between groups in mean cost to the difference in mean QALYs (FIHOAs). By means of bootstrapping, cost-effectiveness acceptability curves (CEACs) were used to consider the uncertainty surrounding the cost-effectiveness of the exercise programme by plotting the probability that exercise programme is cost-effective according to a range of willingness-to-pay thresholds.

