**Secondary outcome measures:**		
Hand pain #	Numeric rating scale (NRS): 0-10	0, 3, 6
Hand stiffness #	Numeric rating scale (NRS): 0-10	0, 3, 6
Patient Global Assessment of disease activity #	NRS: 0-10	0, 3, 6
Patient Global Assessment of disease activity affecting activities of daily living #	NRS: 0-10	0, 3, 6
Patient Global Assessment of change in disease activity over past three months #	7-point scale	3, 6
Patient Global assessment of change in management of activities of daily living #	5 point scale	3, 6
Grip strength (JAMAR dynamometer)	Kilogramme (mean of three repetitions)	0, 3, 6
Hand dexterity (Moberg Pick-up Test [38])	Seconds (right hand, left hand)	0, 3, 6
Thumb web space (Grip Size instrument)	Cylinder size: 1–12 cm	0, 3, 6
Health-related quality of life (15D [39])	0-1 scale	0, 3, 6

*0 = baseline, 3 = 3 months, 6 = 6 months.

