### Secondary outcome measures

A number of secondary measures are used (Table 3), including an 11-point NRS to obtain self-reported hand pain, hand stiffness and Patient Global Assessment of disease activity and disease activity affecting the activities of daily living. To help capture potential changes at the 3- and 6-month follow-up, 7- and 5-point versions of the Patient Global Assessment of Change Scales are used to self-report disease activity and the management of activities of daily living, respectively.

Maximal grip strength is measured using a Jamar Dynamometer. The participant sits on an armless chair with the shoulder in a neutral position and the elbow 90° flexed. A maximal squeeze of the dynamometer is performed three times for each hand with 15 second breaks, and the average values for each hand will be calculated.

A functional performance test, the Moberg Pick-up Test, is included to help obtain a quantitative assessment of hand dexterity [38]. The test consists of 12 small objects that have to be picked up while time is recorded using a stop watch. The standard protocol by Ng et al. is applied, and the test is performed once with each hand and the eyes open. The 12 objects are in accordance with a description in the paper by Stamm et al. [38].

To measure the thumb web space in a standardised manner, a Grip Size instrument (12 transparent plexiglass cylinders with a diameter from 1 cm to 12 cm) is used. Participants are asked to grip one cylinder at a time, and the largest size where the assessor can see full contact between the cylinder and the total arch of the participant’s thumb and second digit is recorded.

The 15D instrument of health-related quality of life (15D) is a generic, comprehensive, self-administered instrument that captures 15 dimensions (i.e. mobility, usual activities, discomfort and symptoms, distress) with five response categories in each dimension, thereby making it theoretically possible to further describe the 30 billion health states [39]. A set of utility or preference weights will be used to generate the 15D score (single index number) on a 0–1 scale, which will be used as a utility measure in the cost-utility analysis.

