### Statistical analyses

#### Data analysis

Demographic and clinical characteristics as well as other baseline data are being collected and will be presented to assess the baseline comparability of the two groups. These variables will also be compared for those participants who withdraw from the study and those who remain. Parametric and non-parametric statistical analysis models will be used depending on the distribution of the variables.

The intention-to-treat principle (ITT) will be followed in the primary analyses of data, and will include all participants, also those who have missing data and those who are not fully compliant with the protocol. Descriptive statistics will be presented for each group as the mean change (standard deviation, 95% confidence intervals) in the outcomes from baseline to each time point. Differences in mean change from baseline to each time point will be compared between groups, using linear mixed models or generalised linear regression modeling, adjusting for baseline levels of the outcome measure. Model assumptions will be checked by standard diagnostic plots, and improvements in the intervention and control group based on the perceived ratings of change will be compared using logistic regression, and presented as odds ratios with 95% confidence intervals. Additionally, the number of “responders” in the two groups will be compared using the OMERACT-OARSI responder criteria [54]. A participant will be classified as a responder if one of the following is fulfilled:

1) High improvement:

•≥50% improvement + absolute change of ≥2 in self-reported hand pain (NRS, 0–10), OR

•≥50% improvement + absolute change of ≥6 in self-reported hand activity performance (FIHOA, 0–30);

OR

2) Improvement in at least 2 of the 3 following:

•≥20% improvement + absolute change ≥1 in self-reported hand pain

•≥20% improvement + absolute change ≥1 in Patient Global Assessment of disease activity (NRS, 0–10)

•≥20% improvement + absolute change ≥6 in self-reported hand activity performance (FIHOA)

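### As worded, QALYs use 15D at 3 and 6 months, so months 0–3 have no starting utility; separately, no baseline adjustment of the QALY difference is stated

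*Protocol article*

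**What the plan says.** Under Health economics the protocol article sets the status of the analysis, "The primary economic evaluation will be cost-utility analysis (CUA", and says of its QALYs: "which will be calculated using the 15D scores at 3 and 6 months". The cost per QALY is then defined as "the ratio of the difference between groups in mean cost to the difference in mean QALYs (FIHOAs", with bootstrapping for the acceptability curves.

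The measurement schedule is wider than that sentence. Under Outcome measures: "All outcome measures are collected at baseline, 3 months (post-intervention, primary endpoint) and 6 months (Tables 3 and 4". Table 3 lists 15D at 0, 3 and 6 months, and the text on secondary outcomes says of the 15D score: "which will be used as a utility measure in the cost-utility analysis".

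Under Data analysis, change in the clinical outcomes is compared between groups "adjusting for baseline levels of the outcome measure". The Health economics section neither refers to that rule nor states one of its own.

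**The concern.** The sentence on QALYs names its inputs and leaves out one that the trial collects. Two consequences follow, and they have different causes.

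- **Valuation of months 0–3.** A QALY over six months needs a utility at the start. Without it, the first half of the horizon is either left out or valued at the post-intervention level. The 12-week programme runs in exactly this half, so its group-session and telephone costs enter the numerator while the health gained alongside them is uncounted or overcounted.
- **Baseline imbalance.** An unadjusted difference in mean QALYs carries any chance difference in baseline 15D into the denominator of the cost per QALY and into the acceptability curve. This comes from the missing adjustment, not from the choice of time points.

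**Working it through.** **Figures in the plan.** The article gives no 15D mean, SD, correlation or effect and no QALY figure, so there is none to reproduce. The group size comes from the Sample size section. Its calculation reproduces: 2 × (1.960 + 0.842)² × 6.2² / 3² = 67.1, rounded up to 68, with 75 per group planned after the drop-out allowance. It matters here only as the source of n = 75.

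**Step 1: months 0–3.** Let u0, u3 and u6 be the between-arm 15D differences at 0, 3 and 6 months. Each interval is 0.25 year. Take u0 = 0 and u3 = u6 = d.

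| Construction | Formula | Result | Against 0–3–6 area | d = 0.02 (assumed) |
|---|---|---|---|---|
| Area over 0, 3, 6 | 0.125(u0+u3) + 0.125(u3+u6) | 0.375d | – | 0.0075 |
| Months 3–6 only | 0.125(u3+u6) | 0.25d | −33% | 0.0050 |
| 3-month score carried back | 0.25u3 + 0.125(u3+u6) | 0.50d | +33% | 0.0100 |

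The percentages do not depend on d. With an assumed cost difference of 300 units and d = 0.02, the cost per QALY is 40,000, 60,000 and 30,000 in turn, so the two literal readings differ twofold. If the effect is gone by month 6 (u6 = 0), the three results are 0.25d, 0.125d and 0.375d, and the error is ±50%.

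**Step 2: chance imbalance.** Assume a 15D SD of 0.10, correlation 0.8 between any two visits, 75 per arm and no treatment effect.

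- SE of the baseline difference: 0.10 × √(2/75) = 0.0163.
- A 1-SE imbalance is expected to persist at 0.8 × 0.0163 = 0.0131 at 3 and 6 months.
- Carry-back: 0.50 × 0.0131 = 0.0065 QALY.
- Months 3–6 only: 0.25 × 0.0131 = 0.0033 QALY.
- Over an assumed SD of 0.08 to 0.12 (baseline SE 0.0131 to 0.0196), the ranges are 0.0052 to 0.0078 and 0.0026 to 0.0039.

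**Step 3: what removes the imbalance.** Under the same assumptions:

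- Adding baseline to the area without adjustment, the 1-SE shift is 0.125 × 0.0163 + 0.375 × 0.0131 = 0.0069, no smaller than under carry-back.
- SE of the unadjusted 0–3–6 area (weights 0.125, 0.25, 0.125): √(0.09375 + 2 × 0.8 × 0.078125) × 0.0163 = √0.21875 × 0.0163 = 0.0076.
- SE of the same area after regression on baseline (residual variance 1 − 0.8² = 0.36, residual covariance 0.8 − 0.8² = 0.16): √(0.25² × 0.36 + 0.125² × 0.36 + 2 × 0.25 × 0.125 × 0.16) × 0.0163 = √0.038125 × 0.0163 = 0.0032.
- SE unadjusted for months 3–6 only: √0.05625 × 0.0163 = 0.0039. For carry-back: √0.23125 × 0.0163 = 0.0079.

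These quantities estimate different multiples of d, so precision must be compared per unit of d. Months 3–6 only gives 0.00387/0.25 = 0.0155; carry-back 0.00785/0.50 = 0.0157; unadjusted area 0.00764/0.375 = 0.0204; adjusted area 0.00319/0.375 = 0.0085. From 0.0155 to 0.0085 is a fall of about 45%, and it comes from the regression, not from the extra time point.

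**The case against.** The strongest reply is that the sentence is shorthand. It gives no QALY formula and no rule for months 0–3, and it does not say that only those two scores are used. The authors may have meant follow-up to 3 and 6 months, with baseline taken for granted. This stands as a limit on confidence. It does not make the wording safe, because an analyst could follow it as written and the missing adjustment would remain.

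A second reply is that a difference in mean QALYs is the ordinary verbal definition of the increment. It does not exclude estimation by regression, and covariates may be left to a fuller plan. That is fair, and it makes the second part weaker than the first. But the article does state its inputs and its estimator, and its baseline-adjustment rule is written for change in outcomes. A QALY accrues over time and has no baseline level of its own, so the rule does not carry over without being restated.

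Four stronger inferences are tempting and are not supported:

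- **That leaving baseline out of the area lets the imbalance in.** Step 3 shows that the unadjusted 0–3–6 area is just as exposed.
- **That the fix cuts the SE by the ratio of two raw SEs.** Those SEs are on different scales. The like-for-like fall is about 45%.
- **That a 1-SE imbalance moves the result by 0.0082 QALY (0.5 × 0.0163).** That needs full persistence. At correlation 0.8 it is 0.0065 at most under the two literal readings.
- **That imbalance will decide the sign of the denominator.** With d = 0.02 under carry-back, an adverse imbalance of 0.0100/0.0065, about 1.5 SE, would be needed. This is possible, but it rests wholly on assumed values.

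**Conclusion.** The point holds as two separate defects in the stated specification. Read literally, the QALY gain is misvalued by −33% or +33% for an effect that builds linearly to month 3 and then holds. The direction depends on a construction that the article does not give. Independently, no baseline adjustment is stated for the QALY difference. A 1-SE chance imbalance would then shift it by about 0.003 to 0.0065 QALY under SD 0.10, correlation 0.8 and 75 per arm, against 0.0075 QALY for a true 15D effect of 0.02.

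The percentages rest on the assumed shape of the effect, and the QALY figures on assumed 15D values, since the article supplies none. A reader might conclude that the authors chose to exclude baseline; the sentence may equally be loosely worded, and confidence on that is moderate. The FIHOA/PSFS primary analysis, the sample size and the data collection are untouched. The change is worth making before the economic analysis is run.

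**What to change.** Reword the QALY sentence under Health economics to make two statements:

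1. QALYs are the area under each participant's 15D curve over 0, 3 and 6 months by the trapezoid rule: 0.125(u0+u3) + 0.125(u3+u6), with u now the participant's own score.
2. The incremental QALY is the group coefficient from a regression of QALYs on group and baseline 15D, refitted within each bootstrap sample that feeds the acceptability curves.

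Both are needed: the first corrects the valuation of months 0–3, and the second deals with imbalance. If baseline was always meant to be included, the first is a clarification only.

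The cost is a few lines of text and code. Baseline 15D is already scheduled, so no new data are required, and the article already undertakes to document and justify changes to the analysis plan.
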